#### Phase II: external validation-comparative study

2.3.2

The goal of the second phase of the task was to comparatively confirm the diagnostic accuracy of the additional diagnostic assessment using the AI models built in the first phase to assist clinicians in diagnostic assessment. We categorised clinicians into residents, attending physicians and chief physicians according to their experience level. We asked clinicians in the control group to independently judge these influenza cases without the assistance of the AI model; while clinicians in the experimental group did the diagnostic assessment of these influenza cases with the assistance of the AI model. Under this comparison, the metrics of AUC, sensitivity, specificity, and diagnostic consumption time are what are used to initially evaluate the performance of the AI model. Imagine the exciting news that an AI model-assisted clinician can complete a diagnostic assessment with 95% accuracy in just 10 minutes. This dual assessment framework quantifies the added value of AI models in the real world.

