#### Phase III: multi-reader, multi-case validation

2.3.3

Phase 3 used a two-round diagnostic design for evaluating the impact of AI model assistance on the effectiveness of clinician decision-making. The AI models used in Phase 3 were calibrated in the Phase 2 validation phase. Recruited clinicians are split into two rounds subsequently evaluating cases independently then filling in the diagnosis.

The first round of tasks that clinicians receive is the baseline diagnostic assessment. In the baseline diagnostic assessment, clinicians are required to evaluate cases using a standard influenza diagnostic protocol and subsequently complete the diagnostic results.

The second round of tasks allows clinicians to access the risk scores and key influencing factor scores generated by the AI model to fill in the diagnosis during the evaluation of the case.

All clinicians were required to undergo two rounds of tasks. This was done with reference to a previous study (22). The use of machine-assisted diagnosis by clinicians can increase their productivity (23). To minimise bias, cases are randomly reordered between rounds of assessment and a 4-week washout period is set between assessments to reduce recall effects. Diagnostic accuracy (measured as AUC) and clinician confidence (scored on a 5-point Likert scale) will be compared between rounds of assessment to quantify the impact of the model on decision consistency and clinician certainty. This multi-reader, multi-case framework ensures robust assessment of AI-human collaboration while addressing variations in real-world clinical work.

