#### Phase IV: randomized controlled trial

2.3.4

This phase is a pragmatic randomised controlled design to assess the effectiveness of AI-assisted diagnosis in the real world. Clinicians will be assigned in a 1:1 ratio to either the control group (using standard clinical assessment protocols) or the AI model-assisted group. Allocation will be by block group randomisation, stratified by hospital level (urban vs. rural) and clinician experience level (resident, attending, chief) to ensure balanced representation in key subgroups.

The control group will rely exclusively on routine diagnostic workflows, while the model-assisted group will integrate AI outputs into their decision-making process and retain full authority to accept or reject recommendations. The primary outcome is the between-group AUC difference, with a ΔAUC greater than 0.15 defined as clinically significant, which is consistent with the U.S. Food and Drug Administration’s (FDA) benchmarks for diagnostic tools based on artificial intelligence or machine learning (AI/ML). The design simulates real-world clinical practice and quantifies the added value of AI in improving diagnostic accuracy while preserving clinician autonomy.

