#### Primary outcome

2.4.1

As the ultimate goal of this clinical trial is to create highly accurate AI models. Therefore the primary outcome metric was set as the area under the curve (AUC) (25). The AUC quantifies the discriminatory ability of the AI model so that it can distinguish patients who may develop severe influenza from those who will not. Since calculating the AUC requires the use of sensitivity, specificity, true positive rate, true negative rate, false positive rate, and false negative rate, more details describing these results can be found in our separate studies (16, 20).

To account for differences in diagnostic assessments after multiple clinicians read the cases, we planned to use the Dorfman-Berbaum-Metz (DBM) method. The DBM adjusts for differences in diagnostic assessments by clinicians so that AUC difference values between the two groups can be estimated (22). ROC curves were calculated using the pROC (version 1.18.0) software package (28). The AUC values as well as their 95% confidence intervals will then be calculated using MRMCaov (version 0.2.1) (27). For differences between the experimental and control groups, we expected to use the Mann-Whitney U test (29). Clinically significant improvement was defined as an AUC difference between the experimental and control groups greater than 0.15. The null hypothesis here is that the AUC difference is less than 0.7, and the AI model has no discriminatory power. Our method of using AUC to set thresholds not only follows statistical patterns, but is also highly compliant with the criteria for the development of AI-driven diagnostic tools.

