#### Calculation rationale

2.5.1

The sample size was determined based on the primary outcome (AUC comparison between model-assisted and clinician-only diagnoses) using a two-group superiority design. Key parameters were derived from prior studies on AI diagnostic tools (31, 32):

Expected effect size: ΔAUC = 0.15 (clinically meaningful improvement).

Type I error (*α*): 0.05 (two-tailed).

Power (1-*β*): 0.95.

Attrition rate: 20% adjustment for patient dropout or incomplete data.

The minimum sample size for AUC comparison was calculated using the following formula (33):

$$n=\frac{{\left(Z_{1-\alpha /2}+Z_{1-\beta }\right)}^{2}\times [\mathrm{AU}C_{1}(1-\mathrm{AU}C_{1})+\mathrm{AU}C_{2}(1-\mathrm{AU}C_{2})]}{{\left(\mathrm{AU}C_{1}-\mathrm{AU}C_{2}\right)}^{2}}$$

Where:

$\mathrm{AU}C_{1}$
 (model-assisted): 0.85 (34).

$\mathrm{AU}C_{2}$
 (clinician-only): 0.70 (null hypothesis).

$Z_{1-\alpha /2}$
= 1.96, 
$Z_{1-\beta }$
= 1.645.

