#### Justification

2.5.4

The patient sample size was determined through a power analysis to ensure ≥80% statistical power for detecting a clinically meaningful improvement (ΔAUC more than 0.15) in diagnostic accuracy, aligning with FDA guidelines for validating AI-driven medical devices (36).

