#### Primary outcome analysis

2.8.1

The AUC will serve as the primary metric to evaluate the diagnostic accuracy of the AI model. To account for variability inherent in multi-reader, multi-case study designs, the DBM method will be employed, which adjusts for differences in clinician interpretations and case complexity. Analyses will be conducted using the MRMCaov (v0.2.1) and pROC (v1.18.0) packages in R, generating AUC values with 95% confidence intervals (CIs) derived from non-parametric bootstrapping (1,000 iterations). A clinically significant improvement is predefined as a ΔAUC more than 0.15 between the model-assisted and control groups, with the null hypothesis assuming no discriminative capacity (AUC less than 0.70, equivalent to random guessing). This approach ensures robust statistical inference while addressing real-world diagnostic variability across clinicians and settings. Hyperparameter optimization was conducted via Bayesian optimization with 5-fold cross-validation, prioritizing AUC on the validation set.

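### Phase IV names the between-group ΔAUC as primary, but the primary outcome, sample size and primary analysis sections do not confine it to that randomised comparison

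*Protocol article*

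**What the plan says.** Three phases of the Protocol article compare AUC with and without AI assistance.

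- **Phase II (2.3.2).** A control group judges cases unaided, while "clinicians in the experimental group did the diagnostic assessment of these influenza cases with the assistance of the AI model". AUC is one of several metrics. No random allocation is described.
- **Phase III (2.3.3).** The same clinicians read cases unaided in round one and with the model in round two: "Diagnostic accuracy (measured as AUC) and clinician confidence (scored on a 5-point Likert scale) will be compared between rounds of assessment".
- **Phase IV (2.3.4).** Clinicians are randomised 1:1, and here the text says: "The primary outcome is the between-group AUC difference, with a ΔAUC greater than 0.15 defined as clinically significant".

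The trial-level sections are written separately from the phases.

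- **2.4.1 Primary outcome** gives the criterion as "Clinically significant improvement was defined as an AUC difference between the experimental and control groups greater than 0.15". It names no phase and cites both the Dorfman-Berbaum-Metz (DBM) method and a Mann-Whitney U test.
- **2.8.1 Primary outcome analysis** also names no phase. It states the criterion between the model-assisted and control groups, and introduces its method with "To account for variability inherent in multi-reader, multi-case study designs, the DBM method will be employed".
- **2.5.1** sizes the primary comparison as a two-group superiority design, at two-tailed α of 0.05, without naming a phase.
- **2.5.3** says the 348 patients include both retrospective (2019–2024) and prospective (2025) cohorts.
- **2.7.2** assigns retrospective data to Phases I–II and prospective data to Phases III–V.

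**The concern.** A reader who starts from 2.4.1, 2.5 and 2.8.1 cannot tell that the confirmatory comparison is the randomised one and nothing else. The group label, the method and the patient count point to different phases.

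Two things are at stake. The first is the causal reading. Phase II describes no randomisation, so a difference there may reflect which clinicians were assisted. In Phase III assistance always comes second, so any learning or order effect adds to the effect of assistance. The case reordering and 4-week washout are aimed at recall and do not separate order from assistance. The second is selective claiming. If the sections do not say which dataset answers the primary question, a favourable difference from Phase II or III could be reported as meeting the 0.15 criterion. A later analysis plan would have to choose among conflicting statements; it could not simply fill in detail.

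**Working it through.** **Step 1. Which phase does each governing statement describe?**

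| Section | Feature | Phase it fits |
|---|---|---|
| 2.3.4 | ΔAUC > 0.15 called the primary outcome | IV |
| 2.4.1 | groups called 'experimental' and 'control' | II (only 2.3.2 calls the assisted arm 'experimental') |
| 2.4.1 | DBM plus Mann-Whitney U test | no phase named |
| 2.5.1 | two-group superiority design | II or IV, not III (same clinicians, two rounds) |
| 2.5.2 | 109 clinicians per group, citing cluster-randomised methodology | IV |
| 2.5.3 | 348 patients, retrospective plus prospective | retrospective part: I–II by 2.7.2 |
| 2.8.1 | 'model-assisted' and 'control' groups | IV |
| 2.8.1 | multi-reader, multi-case design | title of III |

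The rows do not describe one comparison. The patient count is the firmest conflict: by the protocol's own map (2.7.2), Phase IV is prospective, so retrospective patients among the 348 cannot be Phase IV patients.

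**Step 2. What this does to the power of Phase IV.** Inputs from 2.5.1: AUCs 0.85 and 0.70, two-sided α 0.05. The variance term is 0.85 × 0.15 + 0.70 × 0.30 = 0.3375. Inverting the protocol's formula, power = Φ(0.15 / √(0.3375/n) − 1.96).

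The plan's own figure first: (1.96 + 1.645)² × 0.3375 / 0.15² = 194.9, so 195 per group, against the stated 145. The stated number does not reproduce. That is a separate matter and this point does not depend on it.

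Taking the stated 174 per group as given, and assuming a share of them is prospective (the document gives no share):

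- all 174: Φ(3.406 − 1.96) = 92.6%
- three quarters, 130.5: Φ(2.950 − 1.96) = 83.9%
- half, 87: Φ(2.408 − 1.96) = 67.3%
- one quarter, 43.5: Φ(1.703 − 1.96) = 39.9%

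These ignore attrition and clustering by clinician or hospital. They are illustrative and show only that the split matters.

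**Step 3. Can an error rate be attached?** Only under rules the protocol does not state.

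- If Phases II, III and IV were each tested at two-sided 5% and any one could carry the claim, independence gives 1 − 0.95³ = 14.3%. By simulation it is about 13.6%, 12.5% and 10.9% at assumed correlations of 0.3, 0.5 and 0.7.
- If the rule were simply an observed ΔAUC above 0.15, with both AUCs at 0.70 and an assumed 145 per group in every phase, SE = √(2 × 0.70 × 0.30 / 145) = 0.0538. Then P(Z > 2.79) = 0.3% per phase, and about 0.8% over three independent phases.
- With the 145 split evenly over three phases (48.3 each, assumed), SE = 0.0932 and P(Z > 1.61) = 5.4% per phase, about 15% over three.

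The answer runs from under 1% to about 15%, depending on assumptions the document does not settle. None of these figures covers bias from lack of randomisation or fixed order.

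**The case against.** The strongest reply is that the protocol does name the comparison. Section 2.3.4 is the only phase description to call ΔAUC the primary outcome, 2.8.1 uses the labels of the randomised arms, and 2.5.2 sizes clinicians with cluster-randomised methodology. No text applies the 0.15 threshold to Phase II or III: Phase II uses AUC for an initial evaluation, and Phase III looks at the model's effect on consistency and certainty. Ranking phases as confirmatory or supportive is also often left to an analysis plan, and this is a condensed article.

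Most of this stands. A reader might infer that the primary claim is tied to no phase at all, or that the plan allows three confirmatory tests with a 14.3% false-positive risk. The documents support neither. Phase IV is named, and three such tests are never described.

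The reply does not remove the conflict in 2.4.1, 2.5.3 and 2.8.1. Those sections make positive statements about labels, method and patients that do not fit Phase IV alone. The complaint therefore concerns what is stated, and does not rest on detail left to another document.

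A further tempting step is to reserve the multi-reader method for Phase III. That would be a mistake. Section 2.4.1 introduces DBM to handle differences between the clinicians who read cases, a problem Phase IV shares. Removing it would take away the only stated allowance for reader variability in the randomised comparison.

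**Conclusion.** The point holds in a limited form. Phase IV appears to be the intended home of the primary test, but the primary outcome, sample size and primary analysis sections do not confine it there and are partly written for other designs. That non-randomised data could enter or carry the claim is an inference from this inconsistency.

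The size cannot be put as one error rate. The conflict over patients is concrete: an unstated part of the 348 lies outside Phase IV on the protocol's own data map, and the power of the randomised comparison is unknown until that part is given. The sponsor should correct this before the phases report. The conclusion rests on reading 2.7.2 as the map from data to phases, and on 2.3.2 describing no randomisation. The absence of a description does not prove that Phase II allocation is non-random.

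**What to change.** - **2.4.1 and 2.8.1:** state that the confirmatory ΔAUC test is made once, in Phase IV, between the randomised model-assisted and control groups, using a method that accounts for clinician (reader) variability in that design.
- **Same sections:** state that AUC differences from Phases II, III and V are supportive estimates with 95% confidence intervals and cannot establish the primary claim.
- **2.4.1:** replace 'experimental' with 'model-assisted'.
- **2.5:** state which of the 348 patients belong to the Phase IV comparison, and restate its power if retrospective patients are excluded.

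The cost is a few sentences and one recalculation. A favourable Phase II or III result could no longer be presented as meeting the primary outcome, and the stated power for Phase IV may become less favourable.

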**Significance:**

Our expected result is that the developed model of severe influenza can be more accurate and have a lower misdiagnosis rate than traditional clinical assessment. The pre-specified AUC was 0.18 (95% CI: 0.14-0.22), with an expected 32% reduction in misdiagnosis. The model’s performance was consistent across patients in older adults, underlying disease, and resource-poor areas. The added value of the study is that it is effective in improving early recognition of severe influenza.

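### The primary null hypothesis is misstated in sections 2.4.1 and 2.8.1, does not match the test that section 2.5.1 sizes, and the role of ΔAUC > 0.15 is left open

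*Protocol article*

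**What the plan says.** The protocol article describes the null for the primary outcome in three places.

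- Section 2.4.1 (Primary outcome): "The null hypothesis here is that the AUC difference is less than 0.7, and the AI model has no discriminatory power".
- Section 2.8.1 (Primary outcome analysis): "with the null hypothesis assuming no discriminative capacity (AUC less than 0.70, equivalent to random guessing".
- Section 2.5.1 (Calculation rationale), in the list of formula inputs: "clinician-only): 0.70 (null hypothesis". The other arm is "model-assisted): 0.85 (34". The design is named as two-group superiority with two-tailed α of 0.05 and power of 0.95.

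Section 2.3.4 (Phase IV) makes the between-group AUC difference the primary outcome of the randomised phase.

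The value 0.15 has several roles. Section 2.5.1 plans on it: "Expected effect size: ΔAUC = 0.15 (clinically meaningful improvement". Section 2.4.1 uses it as a threshold: "Clinically significant improvement was defined as an AUC difference between the experimental and control groups greater than 0.15". Section 2.8.1 does the same: "A clinically significant improvement is predefined as a ΔAUC more than 0.15 between the model-assisted and control groups". Section 2.3.4 repeats the threshold, the end of the Introduction makes Δ > 0.15 part of the study hypothesis, and section 2.5.4 claims at least 80% power for an improvement above 0.15.

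The Significance paragraph of the abstract adds: "The pre-specified AUC was 0.18 (95% CI: 0.14-0.22), with an expected 32% reduction in misdiagnosis".

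**The concern.** The null fixes what a significant result means. Here the two sections that define the primary outcome and its analysis give nulls about different quantities: one about a difference between arms, the other about the AUC of one arm. Neither is the hypothesis that the sample size formula tests. The same data could be read as failure under section 2.4.1 and as success under section 2.8.1, and the choice between them could be made after the results are known.

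The threshold adds a second ambiguity. The trial is planned on a true difference of 0.15, and the improvement that counts as clinically significant must exceed 0.15. That is harmless if 0.15 only helps to interpret the result. If it is a bar that the result must clear, the stated power does not apply to it.

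**Working it through.** **Inputs.** From section 2.5.1: AUC1 = 0.85, AUC2 = 0.70, planned difference 0.15, Z values 1.96 and 1.645. From section 2.5.2: 145 per group before the attrition allowance, 174 after it. From the abstract: 0.18 (0.14 to 0.22).

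**The plan's own figure.** The variance term is 0.85 × 0.15 + 0.70 × 0.30 = 0.1275 + 0.2100 = 0.3375. The formula gives n = (1.96 + 1.645)² × 0.3375 / 0.15² = 194.9, so 195 per group. The stated 145 is not reproduced. That is a separate matter. What counts here is the form of the formula: its denominator is (AUC1 − AUC2)² with no margin subtracted, so it sizes a test of difference = 0. With a margin of 0.15 the denominator would be (0.15 − 0.15)² = 0 and no finite sample would do.

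**The null in section 2.4.1.** With a control AUC of 0.70, the largest possible difference is 1 − 0.70 = 0.30. A difference above 0.7 would need a control AUC below 1 − 0.7 = 0.30, far worse than chance. The planned effect (0.15) and the abstract's 0.18 both lie inside this null.

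**The null in section 2.8.1.** An uninformative classifier has AUC 0.50, not 0.70. A statement about one AUC also makes no comparison with control. If both arms had an AUC of 0.85, the difference would be 0 and AI would add nothing, yet this null would be false and could be rejected.

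**The 0.15 threshold, if it were a bar.** Use a normal approximation with SE = √(0.3375 / n). At the planned 145 evaluable per arm, SE = 0.0482.

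| True difference | Estimate > 0.15 | Lower 95% limit > 0.15 | Lower 95% limit > 0 |
|---|---|---|---|
| 0.15 | Φ(0) = 50% | Φ(−1.96) = 2.5% | Φ(0.15/0.0482 − 1.96) = 87.5% |
| 0.18 | Φ(0.03/0.0482) = 73% | Φ(0.03/0.0482 − 1.96) = 9% | 96% |

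The 50% and 2.5% hold at any sample size and for any variance under the normal approximation. The other entries depend on the plan's variance.

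**The abstract interval.** Its half-width is (0.22 − 0.14)/2 = 0.04. The plan's unpaired variance at 145 per arm gives 1.96 × 0.0482 = 0.095.

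**The case against.** The strongest defence is that section 2.5.1 already contains a workable design: two-group superiority, two-sided 5%, planned on the smallest important difference and tested against zero. Sections 2.4.1 and 2.8.1 add an estimate of the AUC difference by the Dorfman-Berbaum-Metz method and AUCs with 95% confidence intervals. On that view, the difference in section 2.4.1 is a slip for the single AUC in section 2.8.1, and 0.15 is a benchmark. Part of this stands, and it rules out four stronger readings.

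- A reader might infer that the trial is declared positive only if ΔAUC exceeds 0.15, so that its real power is 50% or 2.5%. The documents do not support this. Sections 2.3.4, 2.4.1 and 2.8.1 call the threshold clinically significant and not a success criterion. Only the Introduction and section 2.5.4 lean towards a bar. The figures are therefore conditional.
- A reader might count section 2.5.1 as a third incompatible null. The label there is loose, but it marks the comparator value in a formula that tests difference = 0.
- A reader might call the decision rule unusable. It can be repaired from section 2.5.1. The fault is contradictory text.
- A reader might say that the abstract's interval is impossible. The abstract names no phase, Phase III is paired by reader, and the plan's variance ignores the split between severe and non-severe cases and reader variation. The interval is only narrower than the plan's own unpaired variance implies.

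The slip reading does not rescue the text. Replacing the null in section 2.4.1 by that in section 2.8.1 still misstates chance and still leaves the between-group outcome of section 2.3.4 untested.

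**Conclusion.** The point holds. The null is wrong as written in sections 2.4.1 and 2.8.1. The first cannot be rejected at the planned control AUC. The second can be rejected without any benefit of AI over unaided clinicians. Neither matches the test of difference = 0 that section 2.5.1 sizes. These conclusions follow from the text and from the range of an AUC and need no variance assumption.

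The role of 0.15 is unresolved rather than shown to be wrong. If it is a margin, the chance of passing at the planned effect is about 50% or 2.5%, against the 95% of section 2.5.1 or the at least 80% of section 2.5.4. At a true 0.18 it is about 73% or 9%, given 145 evaluable per arm and the plan's variance. If it is a benchmark, no power is lost on this account.

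The abstract's 0.18 is a minor related point. As an AUC it would be worse than chance, so it presumably means an expected difference.

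**What to change.** 1. State one null in sections 2.4.1, 2.5.1 and 2.8.1: AUC(model-assisted) − AUC(control) = 0, two-sided 5%. This matches the existing formula.
2. Delete the null on a difference below 0.7, and the null on an AUC below 0.70 together with its equation to guessing. Keep 0.70 only as the assumed clinician AUC, without the null label.
3. Say in the Introduction and in sections 2.3.4, 2.4.1, 2.5.4 and 2.8.1 that 0.15 is the planning effect and a benchmark for clinical interpretation. A margin would be an equally legitimate choice. If the sponsor wants one, say whether the estimate or the lower confidence limit must exceed it, plan on a true difference above 0.15, and restate the power.
4. In the abstract, label 0.18 as an expected AUC difference, reconcile it with 0.15, and justify or drop its interval.

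With 0.15 as a benchmark, this costs only wording. With 0.15 as a margin, the sample size has to be planned again.
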